### Modification of the protocol

The current protocol version from March 2020 is the protocol the trial was initiated with (protocol version 1.0). In case of protocol amendments, these will be submitted to the ethics committee for approval and no further recruitments will take place until the modifications are accepted.

### Assessment of safety and termination criteria

All adverse events will be documented and analyzed because complications form the study’s primary endpoint in the form of the CCI. Participants will be excluded from the study if they withdraw their consent to participate in the trial. A participant may withdraw consent at any time without explanation and without affecting further medical care. The principal investigator may terminate the trial at any time in consultation with the key research associates and the biostatistician. Possible reasons for termination include high morbidity or mortality rates and any indication of potential health hazards caused by either the study treatment or external factors. In case of intraoperative complications in the minimally invasive group, there might be the need to convert to open surgery. In the case of intraoperatively identifying advanced and irresectable disease, there will be a change to palliative treatment strategies. There are no other criteria for modifying or discontinuing treatment.

### Randomization and blinding

A random allocation sequence has been generated by computer through block-randomization prior to the start of the trial by an independent third party. These allocations have then been put in sequentially numbered, sealed, opaque envelopes and are opened prior to the patient’s surgery. Block sizes of 4, 6, and 8 were used in a variable order. After informed consent, patients will be enrolled by trial-trained physicians and randomized to the intervention or control group on the day before surgery. Allocation is performed by opening these envelopes containing cards displaying “Endoscopic” or “Open.

Blinding of study contributors [39]: No attempt will be done to blind patients and the access sites will be covered with standard wound dressings until discharge. The blinding of the operating surgeon is not possible. The severity of pain and rescue analgesic will be evaluated by anesthesiologists otherwise not involved in the study (data collectors). All cases are reviewed regarding the primary endpoint by a neutral outcome assessor. The statistical analysis will be performed according to the outlined protocol; no additional attempts are made to blind the statistician as this will have no influence on the predefined statistical analysis of previously recorded and saved data.

### Data management

All data will be collected and recorded in case report forms (CRFs) by an investigator before transfer to the data management center. Personal information about potential and enrolled participants will be collected, shared, and maintained with third party only after pseudonymization in order to protect confidentiality. All demographic and baseline clinical data, as well as primary and secondary outcome measures, will be recorded in the CRF. To promote data quality, there will be automated checks for double data entry and value ranges. To ensure patient confidentiality, the CRF for each patient will be given an anonymous allocation number. We will obtain permission to continue follow-up and data collection in the event of withdrawal from the study. The responsible investigator must review and sign all completed CRFs.

### Statistical methods

#### Sample size

The sample size calculation is based on the primary endpoint “postoperative morbidity measured with the CCI until POD 30”. MIVATE is a superiority trial. The null hypothesis claims that the minimally invasive approach is not superior to open surgery in terms of CCI. The alternative hypothesis claims that the minimally invasive approach is superior to open surgery in terms of CCI within POD 30. A decrease of the CCI by 10 points between the minimally invasive and open group is considered relevant by patients and clinicians and a standard deviation of 10 is assumed based on in-house data leading to an effect size *d* of 1.0. There are no studies explicitly indicating the standard deviation of the CCI after esophagectomy.

Based on a *t* test with a two-sided significance level of *α* = 0.05, a sample size of *n* = 34 patients (17 per group) is required in the analysis dataset in order to achieve a power of 80% (calculations performed with Prism 8.0, G*Power and SPSS). To compensate for early trial termination, drop-outs, and loss-to-follow-ups, further 15% of patients will be randomized leading to a total randomization and allocation size of 40 patients (20 per group). The number of patients to be screened and assessed for eligibility (*n* = 200; 100 per group) was calculated with an assumed 20% of exclusions due to exclusion criteria and a 75% of interfering circumstances (200 × 0.8 × 0.25 = 40; 20 per group). These interfering circumstances are due to the fact that MIVATE is an expertise-based trial which only allows the institution’s single best surgeon for each allocated technique. Consequently, both surgeons have to be available at the time of randomization which is not possible in 3 of 4 cases.

Screened and assessed for eligibility (*n* = 200; 100 per group)

Allocated to trial and analyzed for intention-to-treat dataset (*n* = 40; 20 per group)

Per-protocol and as-treated dataset (*n* = 34; 17 per group)

There will be regular meetings by the investigators every 3 months in order to optimize recruitment and ensure sufficient enrolment.

#### Statistical analysis

Superiority of the intervention versus the control will be assessed using a two-sided *t* test. The primary analysis will be based on the intention-to-treat population. If values do not display normal distribution, the Mann-Whitney *U* test will be used. A per protocol and an as treated set will be evaluated as a sensitivity analysis. Missing data for the primary outcome variable will be replaced by using imputation [40]. The primary analysis will test the following hypotheses:
H_0_: CCI_open_ ≤ CCI_minimally invasive_H_1_: CCI_open_ > CCI_minimally invasive_

CCI_open_ and CCI_minimally invasive_ are the mean of the indices of both groups at different time points.

All secondary outcomes will be evaluated descriptively, and descriptive *p* values are reported. All analyses will be done using SPSS, SAS, and R. A detailed statistical analysis plan is developed prior to the analysis of the trial results in order to guarantee for neutrality during the analysis.

There will be no interim analysis for the primary endpoint. However, the primary endpoint will be analyzed as soon as all relevant data has been obtained. There will be interim analyses for the secondary endpoints.

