#### Secondary endpoints

Secondary endpoints can be separated into short-term endpoints and long-term endpoints. Short-term endpoints include operation time, length of hospital stay, duration of stay on intensive or intermediate care unit (ICU), postoperative recovery assessed with QoL-15, postoperative pain assessed with the visual analog scale (VAS), the necessity for vasopressor agents for circulatory support, length of single-lung ventilation, number of days with invasive ventilation, fluid management, postoperative demand for analgesic drugs, and levels of acute-phase proteins in the serum. The successful adherence to an already established fast-track protocol with several sub-categories will also be a secondary endpoint (Additional Tables 1 and 2) [3, 30]. Short-term oncological endpoints are number of removed lymph nodes and rate of R0-resections.

Long-term endpoints are QoL and oncological outcomes such as disease-free-survival, rate of local recurrence and overall-survival. QoL will be assessed with different questionnaires. SF-36 and CAT EORTC QLQ-C30 measure general aspects of health with scores ranging from 0 to 100 and with higher scores representing better well-being. CAT EORTC QLQ-OES18 assesses several aspects of esophageal function, ranging from 0 to 100 with lower scores indicating better function [31].

Extended details of the secondary endpoints can be found in Table 1. Several other scoring systems from other institutions have been included in the design of the MIVATE trail such as the surgical site infection classification according to the CDC (Center for Disease Control and Prevention) (https://www.cdc.gov/hai/ssi/ssi.html) [32], the ASEPSIS score for wound infection [33], and the standardization of data collection for complications associated with esophagectomy from the Esophagectomy Complications Consensus Group (ECCG) [27].

**Table 1 Tab1:** Trial visits

Activity and documentation	Visit 1 (screening)	Visit 2 (surgery)	Visits 3–9 (POD 1–7)	Visit 10 (discharge)	1. Follow-up (POD 30)	2. Follow-up (POD 90)	3.-5. Follow-up (POM 12, 36, 60)
Inclusion and exclusion criteria and informed consent	x						
Biometric data (*1)	X						
Medical history and preoperative assessment (*2)	x						
Oncological baseline data (*3)	x						
Pain with VAS and analgetic management	x	x	x				
ASA, ECOG, Revised Cardiac Risk Index, lung function	x						
Body weight	x				x	x	x
Randomization	x						
Surgery		x					

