**Oncological and specific long-term**							
Histopathological data (*6)				x			
GI symptoms (*7)					x	x	x
Adjuvant therapy					x	x	x
Disease-free survival					x	x	x
Local recurrence					x	x	x
Progression-free survival					x	x	x
Overall survival					x	x	x

(*1) Including age, body height, and sex

(*2) Including medication and previous surgical intervention

(*3) Including first diagnosis, cTNM status, location relative to Z-line, and neoadjuvant chemo- or radiotherapy

(*4) Including surgeons, experience, procedure, operation time, anastomosis, complications, conversion, and drainages

(*5) Including anastomotic leak, conduit necrosis, chyle leak, and vocal cord injury according to ECCG and surgical site infection according to CDC

(*6) Including entity, pTNM, grading and resection status, number of lymph nodes retrieved, and number of tumor positive lymph nodes

(*7) Including dysphagia and reflux

*ASA* American Society of Anesthesiologists classification, *CCI* Comprehensive Complication Index coding complications and related interventions according to the Dindo-Clavien classification, *CDC* Center for Disease Control and Prevention, *CRP* C-reactive protein, *ECCG* Esophagectomy Complications Consensus Group, *ECOG* Eastern Cooperative Oncology Group score, *EORTC QLQ-C30* European Organization for Research and Treatment of Cancer Quality of Life Questionnaire Core 30, *EORTC QLQ-OES18* Computerized adaptive test European Organization for Research and Treatment of Cancer Quality of Life Questionnaire for Esophageal Cancer, *POD* postoperative day, *POM* postoperative month, *QoR-15* Quality of Recovery 15, *SF-36* Short-Form 36, *VAS* visual analog scale of pain. The primary endpoint is displayed in gray

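### The primary CCI test is valid but unadjusted; pre-naming one baseline risk covariate already on the CRF would probably sharpen it at a cost of about one point of power at worst

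*Protocol article*

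**What the plan says.** The Statistical analysis section of the protocol article states: "Superiority of the intervention versus the control will be assessed using a two-sided" *t* test. The fallback is also unadjusted: "If values do not display normal distribution, the Mann-Whitney" *U* test replaces it. On the analysis set: "The primary analysis will be based on the intention-to-treat population". The Sample size section lists this set as 40 patients (20 per group) and the per-protocol and as-treated set as 34 (17 per group).

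The sample size rests on the same unadjusted *t* test, with a "two-sided significance level of *α* = 0.05", a 10-point difference and an SD of 10.

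Table 1 (Trial visits) collects at screening: "ASA, ECOG, Revised Cardiac Risk Index, lung function". Its footnotes add age and sex, and oncological baseline data: "Including first diagnosis, cTNM status, location relative to Z-line, and neoadjuvant chemo- or radiotherapy".

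The Randomization and blinding section describes blocks of 4, 6 and 8 in variable order and names no stratification factor. The Discussion promises a descriptive subgroup analysis of influencing factors. No adjusted analysis of the primary endpoint is mentioned. A detailed statistical analysis plan is announced but not shown.

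**The concern.** With 40 patients, precision is scarce. Any part of the CCI variance that preoperative risk could explain stays in the standard error of a raw comparison. With no named stratification factor, nothing in the stated design or analysis takes account of a chance difference in operative risk between the arms. The planned descriptive subgroup analysis would not change the primary estimate.

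The protocol has reason to value precision. The Sample size section says that no study explicitly gives the SD of CCI after esophagectomy and takes 10 from in-house data. If the true SD is larger, the assumed effect size of 1.0 shrinks and power falls quickly.

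The choice of primary test is stated in the article, so the point is not merely a detail left to the analysis plan.

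**Working it through.** **Inputs from the protocol article (Sample size).** Difference 10, SD 10, so *d* = 1.0; two-sided α = 0.05; 17 per group analysed; 20 per group randomised.

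**Assumed.** R², the share of within-arm CCI variance explained by the covariate. The article gives no value, so a range of 0 to 0.3 is shown.

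**1. The plan's own figure.** For an unadjusted *t* test with *n* per arm, the noncentrality is *d*/√(2/*n*) on 2*n* − 2 degrees of freedom.
- *n* = 17: 1/√(2/17) = 2.915 on 32 df, power 80.7%.
- *n* = 16: power 78.1%. So 17 per arm is the minimum, as stated.
- 34/0.85 = 40 randomised, as stated.
- *n* = 20: 1/√(2/20) = 3.162 on 38 df, power 86.9%.

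**2. Adjustment for *k* covariates.** With N = 2*n*, the noncentrality becomes *d*/√[(1 − R²)(1 + *k*/(N − *k* − 3))(2/*n*)] on N − 2 − *k* df. The middle factor is the expected variance cost of chance imbalance in the covariate. For *k* = 1 it is 1 + 1/36 = 1.028 at N = 40 and 1 + 1/30 = 1.033 at N = 34. Example at N = 40, R² = 0.2: 1/√(0.8 × 1.028 × 0.1) = 3.487 on 37 df, power 92.4%.

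| | Unadjusted | R² = 0 | 0.1 | 0.2 | 0.3 |
|---|---|---|---|---|---|
| 20 per arm, one covariate | 86.9% | 85.9% | 89.3% | 92.4% | 95.3% |
| 17 per arm, one covariate | 80.7% | 79.3% | 83.4% | 87.4% | 91.3% |

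The intention-to-treat set is 40, so the first row is the relevant one if all patients contribute. Imputed outcomes do not carry full information, so the effective size may lie between the two rows.

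**3. Break-even and number of covariates.** At 20 per arm, adjustment pays once R² exceeds about 0.03 with one covariate, 0.06 with two, 0.09 with three and 0.15 with five. With R² = 0, two covariates cost about 2 points at 20 per arm (86.9% to 84.9%) and nearly 3 at 17 per arm (80.7% to 77.9%).

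**4. If the SD were 15 (assumption).** Then *d* = 10/15 = 0.667. At 17 per arm, power is 47.0% unadjusted and 49.7% to 60.0% with one covariate at R² 0.1 to 0.3. Adjustment helps but does not rescue a wrong SD.

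**5. Chance imbalance at 20 per arm.** The standardised difference in a continuous covariate has SD √(2/20) = 0.316, so a gap of 0.5 SD or more has probability 0.11. A binary factor with 30% prevalence differs by 20 percentage points or more with probability 0.23. If R² = 0.2, a 0.5 SD gap shifts the observed CCI difference by 0.5 × √0.2 × 10 = 2.2 points, about a fifth of the 10-point target.

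**6. Choice of standard error.** In a simulation of one normal covariate, 17 per arm, *d* = 1.0 and 8,000 runs, HC3 robust errors lost about 4 points of power against the *t* test at R² = 0 and gained nothing at R² = 0.1. Model-based and HC1 errors lost about 1 point at R² = 0. The small worst-case cost therefore holds only for one covariate with model-based (or HC1) errors.

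**The case against.** The strongest reply is that nothing here is wrong. The unadjusted *t* test is a valid randomised comparison and is the test on which the trial was sized. That stands. A reader might infer that chance imbalance biases the planned test. It does not: randomisation keeps the type I error correct on average, and the standard error already allows for such imbalance. Adjustment reduces the error in the particular trial that was run, and only for the chosen covariate and whatever correlates with it.

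A reader might also infer that the baseline measures are strong predictors and the gain is free. The documents support neither. No correlation with CCI is given. The Discussion attributes 30-day complications mainly to anastomotic insufficiency and pulmonary impairment, which makes lung function a natural candidate but does not measure its value. Each covariate costs a degree of freedom and some variance, so entering all the collected measures could lose power.

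Finally, the absence of stratification is inferred from silence in a condensed article, and the unseen analysis plan may add an adjusted supporting analysis. Both are fair. They do not alter the fact that the stated primary test is unadjusted.

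**Conclusion.** The point holds as a low-cost improvement in precision and in robustness to chance imbalance; it does not correct an error or a bias. With 20 per arm and one covariate, power changes by −1.0, +2.4, +5.5 or +8.4 points at an assumed R² of 0, 0.1, 0.2 or 0.3. With 17 per arm the changes are −1.4, +2.7, +6.7 and +10.6. These figures assume the plan's difference and SD of 10, approximately normal residuals, a single covariate and model-based standard errors. R² is unknown, but since break-even is about 0.03, the uncertainty bears more on the size of the gain than on the advice.

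**What to change.** Before the primary data are analysed, name one baseline covariate from Table 1, for example lung function (stating which measure) or ASA class (coded to use one degree of freedom). Then:

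- Make the primary analysis a linear model of 30-day CCI on randomised arm plus that covariate, in the intention-to-treat set.
- Report the adjusted mean difference with a 95% confidence interval from model-based standard errors.
- If CCI is skewed, take a permutation *p* value for the same adjusted difference, so that the quantity estimated does not change with the shape of the data.
- Keep the unadjusted test as a sensitivity analysis.

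The cost is a sentence or two in the protocol or analysis plan and one degree of freedom, with no new data. The change is still possible under the article's own terms: the analysis plan is to be written before the results are analysed, and no interim analysis of the primary endpoint is planned. If the sponsor prefers to keep the *t* test as primary, the adjusted model should at least be named in advance as a supporting analysis.

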## Discussion

Localized esophageal carcinoma can be treated curatively with surgery, but esophagectomy remains challenging with considerable morbidity and mortality, an extensive recovery period as well as impairment of QoL. In comparison to other major gastrointestinal surgeries, open esophagectomy is associated with high rates of complications of up to 34% of pneumonia as described by Biere et al. in 2012 [41] and up to 19.4% of anastomotic leakage, as well as 15.8% of recurrent laryngeal nerve palsy as described by Booka et al. in 2015 and Asaka et al. in 2019 in case of cervical anastomosis [42, 43]. The overall pulmonary complications are described to be as high as 40.5% for OE compared to 9.5% for MIE (*p* = 0.004) in some studies [44]. Especially pneumonia has a significant negative impact on survival (*p* = 0.035) with a multivariate HR of 1.456 (([CI] [1.020; 2.079]) *p* = 0.039). Therefore, strategies to prevent pneumonia after esophagectomy are assumed to improve postoperative outcomes [42]. The MIVATE trial is the first RCT to compare total MIE versus OE in an expertise-based approach. It focuses on the difference of postoperative complications within 30 postoperative days which are mainly caused by anastomotic insufficiencies and pulmonary impairments. The primary endpoint is the CCI within postoperative day 30 and therefore a highly objective and standardized parameter that will also be suitable in performing sample size calculations for further randomized multicenter trials and thus also enabling large-scale meta-analyses.

The MIVATE trial consist of a complex intervention with two subinterventions: The first and main subintervention is the comparison of the total minimally invasive surgical approach (MIE) compared to the open approach (OE), whereas the second subintervention is the use of two different anastomotic techniques that are specified for each group. The linear stapled anastomotic technique is only used in the MIE group, whereas the circular stapled approach is only used in OE. This is mainly due to practical reasons since the linear stapling technique is facilitated by the minimally invasive access with trocars whereas this technique is more cumbersome in open approach due to angulation and access difficulties. On the other hand, the circular stapling technique is more practical in open surgery whereas in minimally invasive surgery this proves more difficult. This combination of two different steps of intervention leads to the problem that identified differences between the groups can possibly not be ascribed to one specific interventional aspect. However, while complex interventions are not necessarily suited to explain effects mechanistically—which is not the scope of this trial—they are recognized to be more sensitive to differences between groups and to more effectively reflect on reality. Consequently, the advantage of this complex intervention is its ability to screen for several interventional steps at once resulting in an increased probability of difference detection as well as its representative validity of esophageal surgery representing regularly performed operation methods and thereby increasing the relevance and external validity of this trial. Yet, there will be descriptive subgroup analysis to identify potential major influencing factors.

Another strength of the MIVATE trial is the extensive surgical standardization. There is no surgical heterogeneity within the groups as every single patient of one group is treated by the same highly experienced surgeon according to the aforementioned description of expertise-based principles. This reduces bias by ensuring that every patient gets the best surgical expertise available and avoids both the “problem of the poor control group” [45] and poor recruitment. Furthermore, patients follow a highly standardized fast track protocol for postoperative recovery, of which the adherence will be documented and reported.

The MIVATE trial specifically addresses the issue of short-term complications in comparing OE and MIE with two different anastomotic techniques with the intention of making a contribution to an optimized treatment strategy for esophageal cancer. Long-term oncological outcomes will have to be evaluated in further multicenter trials with adequate power.

In summary, this monocenter trial will evaluate the difference between OE and total MIE focusing on postoperative complications. The MIVATE trial will provide further evidence of optimal technique for oncologic esophagectomy comparing the open and total minimally invasive approach. The two singularizing aspects of this trial are the linear stapled anastomosis for total MIE as well as the expertise-based approach. The findings will serve as a basis for conducting multicenter RTCs to evaluate which procedure is best for patients requiring esophagectomy in order to further optimize outcomes and reduce complications.

